### **2.4 Randomization procedures**

To test whether the two approaches are more effective than the standard of care approach in reaching new individuals for HIV testing and linkage to care at GP practices, individuals will be randomized in a 1:1:1 ratio to the three study arms. We will use computer-generated random numbers with stratification on study groups to get an equal number of study groups. After randomisation, brochures related to the specific study groups will be placed in different envelopes. Each envelope will be marked, entail one of three brochures and allocated in advance to the YCN field workers for distribution.

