## **2.5 Recruitment procedures**

Each YCN field worker will use a recruitment script (Appendix 4) to engage with potentially eligible individuals and will then hand them a marked envelope. Individuals will be recruited individually or in groups. The handing out of brochures is a standard demand creation strategy and no informed consent will be obtained from individuals during this interaction. The field worker will only record basic demographics (age group, gender) on individuals who receive the study envelopes on the REDCap system. This will be completely anonymised and not linked to any personal identifying information and only used to determine aggregate statistics. YCN field workers will target areas in the GP's catchment area (or within a local taxi ride) specifically targeting high volume and high transit settings. Some recruitment sites will include the industrial zone/formal workspaces, informal workspaces (trading stalls, spaza's, salons, veggie stalls etc), retail/shopping zones, establishments that sell food, educational settings (TVET, university, trade schools, etc), commuter stops and other community settings (indoor and outdoor venues). We will be able to record which envelopes are distributed at the different recruitment sites on REDCap using the data fields on the distribution log (Appendix 5).

Individuals who are interested in the services provided by the GP and attend the GP practice will be asked about how they heard about the practice and requested to hand-in the brochure that they received. The individual will then be requested to sign a study consent form (Appendix 8 and

9) before any data is collected and sign an HTS consent form (Appendix 7) before any medical procedures. As part of the research study and routine procedures at the GP practice, we will ask participants some questions. Questions will include but are not limited to demographic information (age, gender, telephone number and primary home address) and HTS outcomes (Date of HIV test, HIV test result and ART start date).

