### **1. Distribution of envelopes containing brochures of the different study groups in the community by the YCN field worker**

- Number of envelopes distributed in the community, by study group
- Demographics captured by the field worker of the target population that accepted the envelopes (age, gender)

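### Section 2.4 stratifies on the study arm itself, and pre-issued marked envelopes have no stated order of issue or concealment, so the protocol does not secure the random allocation

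*Protocol*

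**What the plan says.** Section 2.4 states that "individuals will be randomized in a 1:1:1 ratio to the three study arms". The method follows: "We will use computer-generated random numbers with stratification on study groups to get an equal number of study groups". No other stratum or block is named there or elsewhere, although the study uses about five practices (section 2.1) and five field workers over 10 weeks (section 2.7), and each brochure is stamped for a particular practice (section 2.3).

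On the envelopes, section 2.4 adds: "Each envelope will be marked, entail one of three brochures and allocated in advance to the YCN field workers for distribution".

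Section 2.5 describes the hand-out. The worker uses a script "to engage with potentially eligible individuals and will then hand them a marked envelope", and "Individuals will be recruited individually or in groups". Envelopes are logged by recruitment site. Section 2.8 lists as a process measure "Number of envelopes distributed in the community, by study group".

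On contents, section 2.3 gives Groups 1 and 2 their own item on top of the standard-of-care material, whereas section 2.4 puts one of three brochures in each envelope.

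**The concern.** There are two faults of unequal weight.

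The first is a plain error. A stratification factor is something known about a person or place before allocation. The arm is the outcome of allocation, so stratifying on it has no meaning beyond forcing equal totals.

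The second matters more. A computer-generated list protects the comparison only if the next allocation cannot be chosen. Here the allocation takes effect when a worker who holds a stock of envelopes, and has already spoken to the person, hands one over. If the worker can tell the arms apart, people who seem interested can be steered towards one arm. Even without intent, using up one arm's stock before the next would confound arm with recruitment site and calendar time. Calendar time matters because practices serve people for 12 weeks while envelopes go out over 10. Someone recruited on the first day has about 12 weeks to attend, and someone recruited on the last day about 2.

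An analysis plan could not fully repair either problem afterwards. Section 2.5 records only age group and gender at hand-out, so a person's apparent interest would not be available for adjustment.

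**Working it through.** **What the protocol fixes at each step**

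| Step | Stated | Not stated |
|---|---|---|
| Sequence | Computer random numbers, 1:1:1, equal arms (2.4) | Block size; any stratum other than the arm |
| Envelope | Marked, one of three brochures (2.4) | Sealed, opaque, identical, arm-neutral mark |
| Issue to worker | Allocated in advance (2.4) | Ordered stack or serial number |
| Hand-out | After engagement, singly or in groups (2.5) | Order of issue |
| Record | Envelopes logged by site (2.5), counted by group (2.8) | Any check that the order was followed |

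The log shows what was given and where. It does not determine who receives which envelope, and equal counts by arm would look correct even if every envelope had been chosen.

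**Reference scale from the plan.** Section 2.7 claims more than 80% power for a 2-point difference from 5% with 2,400 per arm (two-sided alpha 0.05). This reproduces: 83.1% for 5% v 7%, with 2,213 per arm needed for 80%. At 4,000 per arm the power is 96.5% at a 5% control rate, and it stays at 80% or more up to a control rate of about 10.5%. The larger sample does not protect against bias; it makes a small spurious difference more likely to reach significance.

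**Illustration 1: steering with no true effect (all inputs assumed except n, alpha and the 5% mean).** Suppose 20% of people are keen and attend at 15%, and the rest attend at 2.5%. The mean is 0.20 × 15% + 0.80 × 2.5% = 5%. With keen share s, the arm rate is 0.15s + 0.025(1 − s). The standard error is √[p₁(1 − p₁)/4,000 + p₀(1 − p₀)/4,000], and the rejection probability is that of a two-sided 5% normal test.

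| Keen share, favoured arm v each other arm | Arm rates | Spurious difference | Rejection rate |
|---|---|---|---|
| 22% v 19% | 5.25% v 4.88% | 0.38 points | 12% |
| 24% v 18% | 5.50% v 4.75% | 0.75 points | 33% |
| 25% v 17.5% | 5.63% v 4.69% | 0.94 points | 47% |

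For the first row, the standard error is 0.49 points and z = 0.375/0.490 = 0.77, which gives 12%. An unsteered arm would hold 0.20 × 4,000 = 800 keen people. The rows put 880, 960 and 1,000 in the favoured arm, that is 80, 160 and 200 extra.

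**Illustration 2: a different assumed population.** Half attend at 8% and half at 2% (mean 5%). If the share of likely attenders differs between two arms by d, the spurious difference is 0.06d. For d = 5, 10 and 20 points it is 0.3, 0.6 and 1.2 points, and the rejection rates are about 9%, 23% and 69%.

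**Chance imbalance by worker if the order is truly random.** Assume 12,000 envelopes, 4,000 per arm, split equally so that each of five workers holds 2,400. The expected number per arm per worker is 800. The hypergeometric SD is √[2,400 × (1/3) × (2/3) × (9,600/11,999)] = 20.7, so the 95% range is about 760 to 840. This is small.

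**The case against.** Several points count against a stronger reading, and most of them stand.

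- A reader might infer that workers can see the arm. Steering requires this, and no section says that the mark shows it. Recording which envelopes go to which site is consistent with an individual code.
- A reader might take "brochures related to the specific study groups will be placed in different envelopes" to mean envelopes that look different by arm. The natural meaning is separate envelopes, one per allocation.
- A reader might infer that Group 1 and 2 envelopes are thicker. Section 2.3 allows this, but section 2.4 says one brochure per envelope. Section 1.5 also counts a website, a Facebook page and signage as standard of care, so an addition to it need not be a second sheet.
- A reader might infer that the primary model is unadjusted. Section 2.10 says only logistic regression; covariates may be set in the SAP, which is not shown.
- Some steering could be visible. A skew by age could appear in the recorded age groups if the log links envelope to recipient. Steering on apparent interest would not appear.
- The stratification phrase is arguably a slip, since the same sentence gives its purpose. By itself it causes no bias.
- Section 3.7 promises more detailed operating procedures, and the recruitment script and distribution log (Appendices 4 and 5) are listed but not shown. They may contain an order of issue. However, the protocol does not say that they cover allocation, and they would not correct the sentence in section 2.4.

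What remains is that a team following the visible text exactly could use concealed, ordered envelopes or could let workers choose, and both would comply.

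**Conclusion.** The point holds as a gap in safeguards, not as evidence of bias. Section 2.4 misnames the stratification factor, and sections 2.4 and 2.5 leave open both the order of issue and the concealment of the arm.

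The documents give no basis for the size of any bias. The false-positive rates of 12%, 33% and 47% rest wholly on assumed attendance rates and steering shares. Even the largest spurious difference in that set (0.94 points) is under half the 2-point target. The figures show only that modest steering would matter at 4,000 per arm.

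Missing balance by practice or worker is the minor part. With a truly random order, chance imbalance is small (about 760 to 840 per arm per worker under an equal split). It becomes important only if stock is used in arm batches, which no stated rule forbids. The matter should be settled before envelopes are packed.

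**What to change.** Replace the stratification sentence in section 2.4 with a rule to this effect:

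- allocation 1:1:1 in permuted blocks of varying size (for example 3, 6 and 9) within GP practice or field worker;
- identical, opaque, sealed envelopes carrying only a serial number;
- the list linking serial number to arm held centrally, away from field workers;
- envelopes handed out strictly in serial order, including when people are approached in groups, with each serial logged.

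Reconcile section 2.3 (intervention item on top of standard material) with section 2.4 (one of three brochures). If intervention envelopes do hold an extra item, add a filler sheet to the Group 3 envelopes so that thickness does not reveal the arm.

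If practice becomes a stratum, it would normally also enter the primary model; that can be left to the SAP.

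The cost is a rewritten paragraph, a regenerated list, some extra preparation and the discipline of keeping to the order in the field. No staff are added and the sample size does not change.

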## **2.5 Recruitment procedures**

Each YCN field worker will use a recruitment script (Appendix 4) to engage with potentially eligible individuals and will then hand them a marked envelope. Individuals will be recruited individually or in groups. The handing out of brochures is a standard demand creation strategy and no informed consent will be obtained from individuals during this interaction. The field worker will only record basic demographics (age group, gender) on individuals who receive the study envelopes on the REDCap system. This will be completely anonymised and not linked to any personal identifying information and only used to determine aggregate statistics. YCN field workers will target areas in the GP's catchment area (or within a local taxi ride) specifically targeting high volume and high transit settings. Some recruitment sites will include the industrial zone/formal workspaces, informal workspaces (trading stalls, spaza's, salons, veggie stalls etc), retail/shopping zones, establishments that sell food, educational settings (TVET, university, trade schools, etc), commuter stops and other community settings (indoor and outdoor venues). We will be able to record which envelopes are distributed at the different recruitment sites on REDCap using the data fields on the distribution log (Appendix 5).

Individuals who are interested in the services provided by the GP and attend the GP practice will be asked about how they heard about the practice and requested to hand-in the brochure that they received. The individual will then be requested to sign a study consent form (Appendix 8 and

9) before any data is collected and sign an HTS consent form (Appendix 7) before any medical procedures. As part of the research study and routine procedures at the GP practice, we will ask participants some questions. Questions will include but are not limited to demographic information (age, gender, telephone number and primary home address) and HTS outcomes (Date of HIV test, HIV test result and ART start date).

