## **2.7 Sample size**

We anticipate that about 5% of participants in the standard of care group will present at the GP. This is a conservative assumption based on the experiences of similar campaigns in which individuals are approached in the community. With 2,400 adults randomized to each of the three study arms (total sample size of 7,200 adults), we will have >80% power (alpha=0.05, 2-sided) to detect a difference of at least 2 percentage points in attendance at GP practices.

However, since there is a possibility that a larger proportion of participants in the standard of care group will present at the GP, we have selected a sample size of 4,000 adults per arm (12,000 total) as this will ensure there is 80% power to detect a difference of at least 2 percentage points.

A small difference in the primary outcome would be meaningful given the low cost of the demand creation interventions. With 5 field workers distributing materials over a period of 10

weeks, ), the target of 12,000 adults reached by the field workers can be achieved by enrolling 48 individuals per day (which is feasible given the small amount of time needed to enrol an individual). HTS services at the GP practice will also start at the same time as the field work but will run for a period of 12 weeks. Provision of services at the GP practices will continue for an extra 2 weeks following the end of field work in order to allow individuals with the marketing material to still access HTS.

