## **2.10 Data Analysis**

Primary analysis: We will compare the primary outcome between study arms. We hypothesize that presentation at GP practices will be higher in the two intervention arms than in the standard of care arm. We will test for significant differences in the primary outcome between each of the intervention groups and the standard of care group using logistic regression analyses.

Secondary analyses: We will also compare the secondary outcomes in each intervention group to the standard of care group using logistic regression analyses. Our hypothesis is that HIV testing uptake will be higher in the intervention groups than the standard of care group.

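### Handing individually randomised envelopes to people in groups may show controls the other arms' offers and pull both comparisons towards zero

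*Protocol*

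**What the plan says.** **Allocation.** Protocol section 2.4 states that "individuals will be randomized in a 1:1:1 ratio to the three study arms". The envelopes are packed beforehand and "allocated in advance to the YCN field workers for distribution". Under section 2.3, both intervention arms receive their brochure or voucher on top of the standard material.

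**Hand-out.** Section 2.5 says "Individuals will be recruited individually or in groups". Field workers go to shared places such as workplaces, stalls, colleges and commuter stops, "specifically targeting high volume and high transit settings". On data capture it says "We will be able to record which envelopes are distributed at the different recruitment sites on REDCap"; no identifier for people approached at the same moment is described.

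**Sample size.** Section 2.7 starts from "We anticipate that about 5% of participants in the standard of care group will present at the GP". It gives more than 80% power at 2,400 per arm for a 2-point difference, then raises the sample to 4,000 per arm in case control attendance is higher. It mentions no allowance for exposure across arms.

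**Analysis.** Section 2.10 compares attendance "between each of the intervention groups and the standard of care group using logistic regression analyses".

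**Monitoring.** Section 2.5 has attenders asked how they heard of the practice and asked for their brochure. Section 2.8 counts attenders whose brochure came from a friend or relative, and attenders without a brochure who name an arm's material.

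**The concern.** The unit of randomisation is the person, but the unit of contact may be a group of co-workers, classmates or people in a queue. If three of them open their envelopes together, the one holding only the standard brochure can see the voucher or the health-screen offer next to it. By section 2.3 that extra item is the whole contrast between the arms. The primary outcome is attendance at the practice, so hearing of an offer could be enough to change it.

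On the trial's own hypothesis that the offers attract people, this would raise control attendance and shrink both differences. An offer that works could then be missed, or its effect understated. The section 2.8 counts catch only part of this: a control who saw a neighbour's offer but hands in their own brochure looks like an unexposed control.

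**Working it through.** **1. The plan's own figure.** Inputs from section 2.7: 5% control attendance, a 2-point difference, two-sided alpha 0.05. With p̄ the mean of the two rates,

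power = Φ{ [ (p2 − p1)√n − 1.96√(2p̄(1 − p̄)) ] / √(p1(1 − p1) + p2(1 − p2)) }.

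- 5% v 7%, n = 2,400: 83.1%. The stated power above 80% is right.
- 5% v 7%, n = 4,000: 96.5%.
- 10% v 12%, n = 4,000: 81.6%; 11% v 13%: 78.6%.

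The protocol does not say which higher control rate the 4,000 is meant to cover. I assume 10%, roughly the highest rate at which its 80% claim still holds.

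**2. How often a group mixes arms.** With 1:1:1 individual allocation, a control in a group of m shares it with at least one intervention envelope with probability 1 − (1/3)^(m−1):

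| m | probability |
|---|---|
| 2 | 67% |
| 3 | 89% |
| 5 | 99% |

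**3. Effect on power.** Let c be the share of controls who see an intervention offer, and t the fraction of the 2-point effect they take on. Control attendance becomes p1 + c × t × 2 points, and the intervention rate is unchanged. Neither c nor t is in the protocol; both are assumptions. n = 4,000 per arm.

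| Rates without spillover | c | t | Control rate | Difference (points) | Power |
|---|---|---|---|---|---|
| 5% v 7% | 0 | – | 5.0% | 2.0 | 96% |
| 5% v 7% | 20% | 1 | 5.4% | 1.6 | 84% |
| 5% v 7% | 30% | 1 | 5.6% | 1.4 | 73% |
| 5% v 7% | 20% | 0.5 | 5.2% | 1.8 | 92% |
| 5% v 7% | 30% | 0.5 | 5.3% | 1.7 | 89% |
| 10% v 12% | 0 | – | 10.0% | 2.0 | 82% |
| 10% v 12% | 20% | 1 | 10.4% | 1.6 | 62% |

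At 5% v 7% with full transfer, power is 80.3% at c = 24% and 79.2% at c = 25%, so the design tolerates about a quarter of controls being fully exposed. At 10% v 12% it has almost no room.

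**4. Correlation within groups.** People in a group may decide alike. In a two-arm comparison, positively correlated pairs in the same arm add to the variance of the difference, and pairs in opposite arms subtract from it. Under individual randomisation a pair falls in the same one of the two compared arms with probability 2/9 and in opposite arms with probability 2/9, so the two contributions cancel on average. Simulation agrees. With no effect, 5% attendance, 12,000 people, 3,000 replicates and randomly mixed arms, the unadjusted test rejected 5.1% (groups of 3, assumed correlation 0.1), 4.9% (groups of 3, 0.3) and 4.2% (groups of 5, 0.3) of the time. The simulation error is about √(0.05 × 0.95/3,000) = 0.4 points.

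**The case against.** **Spillover is inferred, not stated.** This stands. The protocol says only that recruitment may be in groups. Group size, the share recruited that way and when envelopes are opened are not given, and a closed envelope is itself a partial barrier. The field worker script and the distribution log (Appendices 4 and 5) are listed by title only and may already deal with some of this.

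**Full transfer is a worst case.** This also stands. The voucher is meant to work through an endowment effect and loss aversion, which plausibly needs the voucher in hand, and controls are already told that testing and treatment are free. Hence the half-transfer rows, where the loss at 5% v 7% is modest. The bias is also towards no difference, so it would not create a false positive. Against this, the extra sample was bought to cover a higher control rate, and that room cannot be spent twice.

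**The analysis plan can handle it.** Only in part. Choice of standard errors and sensitivity analyses can wait for that plan. The hand-out procedure and the recorded data cannot: if no encounter identifier is captured, group encounters cannot be identified later.

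**A stronger reading.** A reader might infer that ordinary logistic regression gives confidence intervals that are too narrow and a raised type I error. That needs whole groups to receive one arm. In that case simulated error was 8% to 19% for groups of 3 to 5 with assumed correlations of 0.1 to 0.3. Nothing in the protocol says envelopes go out in same-arm runs, and under individual randomisation a group of five is all one arm with probability 3 × (1/3)^5 = 1.2%. The documents do not support that reading.

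**Conclusion.** The point holds as a risk of dilution. The protocol permits group hand-out of individually randomised envelopes, shows no safeguard against recipients seeing each other's offers, and describes no record of who was approached together. The cost ranges from slight (89% to 92% power at 5% v 7% with half transfer and 20% to 30% of controls exposed) to serious (62% at 10% v 12% with full transfer and 20% exposed).

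These figures rest on assumed exposure shares, an assumed transfer fraction, an assumed 10% alternative control rate, and offers that do attract people. They make no allowance for intervention recipients who also see the other offer. The validity of the test and of the confidence intervals is not materially in question while arms are mixed within groups. The change should be made, because it is cheap and cannot be made once distribution is over.

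**What to change.** 1. In section 2.5 and the recruitment script, state that each envelope is handed over one to one, with a request to open it later and alone.
2. Add an encounter number to the distribution log, shared by all envelopes given at the same moment.
3. Pre-specify a sensitivity analysis of the primary comparison that excludes group encounters. Clustering standard errors on encounter is optional.

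The cost is one script line, one log field, one extra analysis and a slightly slower hand-out. Section 2.7 calls the pace feasible ("which is feasible given the small amount of time needed to enrol an individual"). Its 48 a day equals 12,000 / (5 workers × 50 days), taking ten five-day weeks. In an assumed 8-hour day that is 480/48 = 10 minutes per person, before travel, refusals and logging. If the script or log already contains items 1 or 2, it is enough to say so in section 2.5.
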